The school year in Germany starts in fall and ends in summer, whereby the first term ends in spring. In previous research from Norway, seasonal differences in cycling to school were observed between fall (52%), winter (3%), and spring (51%) (30) as well as between winter (12%) and summer (22%) (31). Also in Germany, cycling to school decreases in winter (32). Therefore, the implementation of the intervention should start in fall and end in spring (i.e., during the first term of the school year). According to the preparatory and practical phases, individual components will be implemented one after another at the participating secondary schools over a period of 5 months (see Table 3). As implemented components will prepare students for the possibly more difficult (weather) conditions in winter, we do not expect a negative seasonal influence on the effectiveness of the intervention. For example, information about appropriate clothes will be provided during the joint parents', teachers', and students' evening. Furthermore, parents and teachers will be reminded of serving as role models so that the 12- to 15-year-olds learn how to establish a cycling routine regardless of (weather) conditions in winter. Students will feel safer and more confident in dealing with difficult road conditions after participating in the cycle training, which will improve their basic cycling skills and practice them on-road (e.g., handling obstacles and appropriate driving style). The bicycle train will increase the motivation and safety of students through positive experiences when accompanied by and interacting socially with peers instead of cycling to school alone in the darkness. Furthermore, the bicycle train will establish a new social norm (i.e., cycling to school as an activity throughout the whole year, including winter and not only in summer). The intervention will follow a whole-of-school approach as we designed components that will take place before, during (i.e., in art and physical education (PE) lesson), and after school. At each participating secondary school, a person of contact will be defined who will act as a coordinator for implementing the intervention. Furthermore, the person of contact will interact with the responsible implementers at their school (i.e., PE and art teacher) and a researcher as well as the project manager at the Technical University of Munich (TUM) who can be called or e-mailed any time in case of occurring questions or problems. The researcher from TUM will be in touch with the person of contact to organize data collections and the implementation of components, which will be led by the researcher and student assistants from TUM. As our aim was to draft a sustainable intervention, we will provide secondary schools with all materials needed for the replication of the intervention and initiate several collaborations with government facilities (i.e., police) and nongovernmental organizations (e.g., ADAC) free of charge that can be continued after we will have left schools.

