#### Study Design

The main study is planned as a two-arm (i.e., intervention and control group (IG; CG)) three-level cluster (i.e., students in classrooms in schools) RCT (see Figure 4), whereby a simple randomization technique (i.e., flipping a coin) on school-level was chosen. For convenience, the pilot study will follow a quasi-experimental study design as a non-RCT. Directly before and after the implementation of the intervention, a pre- and post-measurement will take place as part of the effect evaluation. Furthermore, the process evaluation will take place during and after the implementation of the intervention. Based on the intraclass correlation coefficient (ICC) of 0.2 calculated for the variance of days per week students cycled to school between the three secondary schools in our concept mapping study (17), we assigned more than one secondary school to the IG and CG. No treatment will be delivered to the CG. In the main study, approximately 255 students belonging to five schools with two classes in grade(s) 7 and/or 8 will be in the IG and CG, respectively. However, approximately 150 students belonging to three schools will be in the IG and 100 students belonging to two schools in the CG when piloting the intervention.

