#### Sample Size Determination

The optimal sample size for our chosen study design in the main study was calculated based on a formula by Rutterford et al. (34). This formula considers the confidence level (97.5%), power (80%), variance of days per week in cycling to school at the individual level [4.1 days (5)], our estimated clinically important difference in treatment means of days per week in cycling to school at the individual level (1.75 days), number of students per secondary school (based on the mean value in our concept mapping study: 51 students), and ICC of days per week students cycled to school at school level [0.2 days (17)]. According to this formula, the required number of students per intervention condition is 231. For the planned pilot study in the first instance, 10% of the main study's calculated sample size is recommended (35, 36) (i.e., 23 students per arm).

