#### Statistical Analysis

To analyze the effectiveness of our intervention, a multiple group analysis considering the treatment factor (IG vs. CG) will be performed in a structural equation modeling using *R*. In this analysis, variances in the number of cycling days to school and MVPA due to belonging to different secondary schools will be considered in the following four levels: (a) repeated measurements for each student, (b) students, in which the repeated measurements are nested, (c) the class, to which each student belongs, and (d) the school, in which classes are nested. Subsequently, potential moderators (e.g., sociodemographic characteristics of the students) will be added to the model, and cycling to school will be regressed onto potential mediators (i.e., autonomy, competence, and relatedness) in levels (b–d). Furthermore, gender will be considered as a covariate in the analysis.

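### The effectiveness model lists measurement, student, class and school levels but no school-by-time or class-by-time variance and no effect parameter; fitted as listed to pre-post change, it would be anti-conservative.

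*Protocol article*

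**What the plan says.** Under Study Design, whole schools are randomised by coin flip, with five schools and about 255 students per arm in the main study. The same section states that "a pre- and post-measurement will take place as part of the effect evaluation".

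Under Sample Size Determination, the trial is sized on one comparison of means. The target is "clinically important difference in treatment means of days per week in cycling to school at the individual level (1.75 days" per week), with an individual-level variance of 4.1, 51 students per school and a school ICC of 0.2. The result is 231 students per arm.

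Under Statistical Analysis, effectiveness is to be assessed by a multiple-group structural equation model contrasting the arms. Variation due to school membership is to be handled in a four-tier hierarchy, of which the first three tiers are "a) repeated measurements for each student, (b) students, in which the repeated measurements are nested, (c) the class, to which each student belongs". The fourth tier is the school. Moderators and mediators are added afterwards. The section does not say whether the effect is a pre-post change, an arm-by-time term or a post comparison. It also does not say whether class and school effects may differ between the two time points.

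**The concern.** Because schools are randomised, the error term of the arm comparison must contain whatever school-to-school variation affects the contrast being tested. If the contrast is change from pre to post, that is the variation between schools in change. The four listed levels name variation in level only.

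The usual way to fit such a nested list is with one effect per school, class and student, each the same at both time points. These effects drop out of a pre-post difference, leaving only the within-student residual as the yardstick. The sample size section allows for clustering with a design effect of 11; the effect test would then contain none. A null intervention could be declared effective much more often than planned. This is separate from the small number of schools and would remain with many more of them.

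The way the outcome is collected makes school-by-time variation plausible. Table 4 measures cycling by recall of a single past school week, and the Measuring Instruments section has whole classes measured together in the same PE lessons. Local conditions in that week therefore act on a class or school jointly, and differently at pre and post.

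**Working it through.** **1. Reproduce the plan's figure.** Inputs from Sample Size Determination: variance 4.1, difference 1.75, 51 students per school, ICC 0.2, power 80%, confidence level printed as 97.5%.

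- Unclustered: n = 2 × (1.96 + 0.8416)² × 4.1 / 1.75² = 21.016 per arm.
- Design effect: 1 + (51 − 1) × 0.2 = 11.
- 21.016 × 11 = 231.17, which gives the printed 231.

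Reading the 97.5% as a two-sided 2.5% test would give 280, and a one-sided 5% test 182. The printed 231 therefore corresponds to a two-sided 5% test. The figure of 5% is inferred in this way, not printed.

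**2. Split the variance.** School: 0.2 × 4.1 = 0.82. Within school: 0.8 × 4.1 = 3.28.

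**3. Assumptions.** The documents give no pre-post correlation. Let r be the correlation of a school's effect between pre and post, and s the within-school student correlation. Both are assumed and varied. Class-by-time variation is set to zero.

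**4. Variance of the arm difference in mean change** (5 schools of 51 students per arm).

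- True: 2 × [2 × 0.82(1 − r) + 2 × 3.28(1 − s)/51] / 5.
- Used when all levels are time-constant: 2 × [2 × 0.82(1 − r) + 2 × 3.28(1 − s)] / 255.

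Example, r = 0.9 and s = 0.5: true 2 × (0.164 + 3.28/51)/5 = 0.0913 (SE 0.302); used 2 × (0.164 + 3.28)/255 = 0.0270 (SE 0.164). The ratio of variances is 3.38, so the standard error is understated by a factor of 1.84. The approximate type I error is P(|Z| > 1.96/1.84) = 29%.

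**5. Does the time-constant model really behave like this?** Two simulated data sets were fitted with school, class and student intercepts and an arm-by-time term. The standard errors were 0.1739 and 0.1697; a two-sample comparison of individual change scores gave 0.1738 and 0.1698. The two analyses are in effect the same test. The mixed-model fits gave convergence warnings, but the agreement is what the algebra predicts.

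**6. Simulated type I error** (20,000 trials per cell), time-constant levels, change contrast:

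| School correlation r (assumed) | s = 0.3 | s = 0.5 | s = 0.7 |
|---|---|---|---|
| 1 | 5% | 5% | 5% |
| 0.99 | 7% | 8% | 10% |
| 0.95 | 15% | 18% | 26% |
| 0.9 | 24% | 29% | 38% |
| 0.8 | 35% | 41% | 50% |
| 0.5 | 51% | 56% | 62% |

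The formula in step 4 agrees with every cell to within about one percentage point. Comparing school mean changes on 8 degrees of freedom, which retains school-by-time variation, gave 4.7-5.1% throughout.

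**The case against.** The strongest reply is that the text does not say what the calculation assumes. A list of nesting levels does not forbid effects that vary over time. A multilevel structural equation model can hold pre and post as separate school-level variables with a free covariance, which would supply the missing component. Nor does the section say that the contrast is change. These are details that a one-paragraph analysis section in a journal article may leave to a fuller document.

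Much of this stands. A reader might infer that the plan ignores clustering and that its false-positive rate far exceeds 5%. The documents do not support that: class and school are explicitly named, time-varying effects are not excluded, and the inflation depends on a correlation that nobody has reported.

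The seasonal figures also prove less than they seem to. The Program Implementation Plan reports that "seasonal differences in cycling to school were observed between fall (52%), winter (3%), and spring (51"%). These are overall prevalences from Norway, and the fall and spring values are nearly equal. A swing shared by all schools cancels between arms; only differences between schools in the swing matter, and these are not reported.

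Two parts of the reply do not carry through. First, the section does specify variance levels for the effectiveness test, and the list omits the one that school randomisation requires for a change contrast. Making repeated measurements the lowest level has little purpose if only the post value is compared. Second, weather is a doubtful remedy. Moderators enter only after the effectiveness model, and weather is documented while accelerometers are worn. The accelerometers are handed out after the questionnaire, so those records do not cover the recalled week.

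**Conclusion.** The point holds conditionally. As listed, the model contains no school-by-time or class-by-time variance and names no effect parameter. If it is fitted with time-constant nested effects and used to compare pre-post change, the school-randomised comparison is tested in effect at student level.

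The size rests on assumed correlations, together with the document's variance, ICC and cluster numbers. Even near-perfect stability of school effects (0.99) gives 7-10%, and 0.8 gives 35-50%. There is no inflation at a correlation of exactly 1, or if the fitted model does let school effects vary over time. Any class-by-time variation would come on top. Because the present wording permits an invalid test of the primary outcome, and of MVPA in the same model, it should be settled before the data are analysed.

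**What to change.** In Statistical Analysis, name the effect and its error term. The simpler version takes the post-measurement of cycling days (and, separately, of MVPA) as outcome, the student's pre-measurement as covariate and arm as a school-level predictor, with random effects for class and school. The school effect then sits in the error term of the arm contrast, and the baseline already collected can add precision.

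If the repeated-measures form is kept, add school-by-time and class-by-time variances and test arm-by-time against the school-by-time variance. Both versions are valid, and the choice between them is the investigators'.

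The cost is a few sentences. No new data are needed. The confidence interval will be wider than the one from time-constant levels, because it will reflect that schools were randomised.

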## Abstract

**Background:** Despite a high rate of bicycle ownership, the prevalence of cycling to school among children and adolescents in Germany has been constantly low. Cycling to school can contribute to meeting the physical activity recommendations, which the majority of children and adolescents in Germany do not meet.

**Methods:** By using intervention mapping, this study protocol describes the systematic planning process of a school-based intervention in Germany aimed to increase the number of days on which students cycle to school and to increase their physical activity levels. To make sure that the intervention will match the needs of students, we conducted a concept mapping study investigating what students need to cycle to school, as perceived by students, parents, and teachers. The logic model of change was based on an integration of the self–determination theory and the social–ecological model. We structured our intervention as two phases, a preparatory phase with weekly components for and a practical phase with a daily repeated component of the targeted behavior. In the 8-week preparatory phase, teachers, parents, and peers will be involved. The content of the 12-week practical phase will involve peers only and was considered promising based on the findings from a systematic review that we conducted to identify the effective strategies of school-based interventions to promote cycling to school among children and adolescents. Overall, our intervention includes 27 behavior change techniques. A researcher, student assistants, teachers, and other collaborators will implement the intervention; a whole-of-school approach with components performed before, during, and after school was chosen. As a study design, we decided to draft a two-arm three-level cluster randomized controlled trial. Both the effect and process evaluation were prepared. In the first instance, approximately 250 students of 12–15 years of age from grade 7 or 8, who attend a secondary school of intermediate or high educational level located in (sub)urban regions in Southern Germany, will pilot the intervention.

**Discussion:** We expect to provide an effective and sustainable intervention for students, which gives insights into the mechanisms of change concerning the behavior of cycling to school and its influence on physical activity levels.

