**Figure 3 F3:**
[figure not shown]
Logic model of change [modified according to (21) (p. 67)]. MVPA, moderate-to-vigorous physical activity.

Based on the social and physical environment, BPNs can be either satisfied or frustrated leading to a certain degree of motivation, which is crucial for the decision process of the students to cycle to school and the influence on total MVPA. Following this logic model of change, Table 1 illustrates the matrix of performance objectives and determinants targeting the promotion of cycling to school.

**Table 1 T1:** Matrix of performance objectives and determinants targeting the promotion of cycling to school.

**Modules**	**Performance objectives**	**Psychological determinants**		
		**Autonomy**	**Competence**	**Relatedness**
A	Researcher communicates to parents and students the purpose and benefits of cycling to school, useful bicycle-related equipment, and feasible mixed methods when living too far away from school.	Students can choose between different options.	Students are aware of the purpose/benefits and solutions to tolerate adverse conditions (e.g., bad weather, heavy schoolbags) when cycling to school.	Students perceive social support.
B	Researcher seeks help from parents and teachers (e.g., parents do not drive their child to school by car, parents/teachers motivate their child/students to cycle to school, parents/teachers are role models for their child/students by cycling to work regardless of the weather condition and wearing a helmet, teachers develop a cycling-to-school-mission-statement).	Students are personally responsible and extensively independent in planning how to get to school.	Students feel empowered to cycle to school when encouraged.	Students perceive a new social norm, social support from parents and teachers, and social cohesion. Students learn how to establish a cycling routine regardless of the weather condition and wear a helmet through the role modeling of parents and teachers.
C	Researcher shows helmet-compatible hairstyle to students and parents.	Students make their own decisions, which helmet-compatible hairstyle they want to do.	Students know, which hairstyles are helmet-compatible, and can do them.	Students establish the new social norm to wear a helmet and receive social support from parents who can help them to do their helmet-compatible hairstyle. Peers serve as role models.

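### As written, the mediator regression can show that students with higher need satisfaction cycle more, but not that the intervention works through the needs

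*Protocol article*

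**What the plan says.** The Abstract expects an intervention that "gives insights into the mechanisms of change concerning the behavior of cycling to school". The Logic Model of Change gives the chain: depending on the environment, "BPNs can be either satisfied or frustrated leading to a certain degree of motivation, which is crucial for the decision process of the students". Table 1 links the intervention's performance objectives to autonomy, competence and relatedness, and Table 4 lists satisfaction of these needs under mediators.

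The Statistical Analysis section fixes the model. For effectiveness, "a multiple group analysis considering the treatment factor (IG vs. CG) will be performed in a structural equation modeling". Four levels are listed, beginning with "a) repeated measurements for each student" and followed by (b) student, (c) class and (d) school. On mediation the section says that "cycling to school will be regressed onto potential mediators (i.e., autonomy, competence, and relatedness) in levels (b–d"). It states no regression of the needs on arm, no comparison of the needs between arms, and no indirect effect. The Discussion adds only that mediators and moderators will be controlled for.

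Under Study Design, "a simple randomization technique (i.e., flipping a coin) on school-level was chosen". Arm is therefore constant within every student, class and school.

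**The concern.** Mediation needs two links: the intervention changes the needs, and change in the needs goes with change in cycling. The plan states only a needs-to-cycling link. It estimates that link from differences between students, classes and schools, with arm as the grouping factor, so the randomised contrast does not enter the coefficient. Students who feel more autonomous, competent or connected about cycling may well cycle more, whatever the intervention did.

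At stake is the mechanism claim. A positive coefficient could be read as support for the self-determination chain although autonomy, competence and relatedness did not move. The reverse error is also possible: real mediation through change within students could be missed.

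**Working it through.** **1. The plan's own figure.** The section gives no figure for mediation. The only computed figure is the sample size, used here to confirm the inputs (Sample Size Determination: variance 4.1, difference 1.75 days, 51 students per school, ICC 0.2):

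2 × (1.960 + 0.842)² × 4.1 / 1.75² = 21.016; × [1 + (51 − 1) × 0.2] = 21.016 × 11 = 231.2 per arm.

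This matches the stated 231. Nothing below changes it.

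**2. What the coefficient contains.** For student *i* in arm *g* (0 or 1), write the need as T_i + e_i0 before and T_i + a·g + e_i1 after, where *a* is the intervention effect on the need.

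- Student average: T_i + a·g/2 + mean(e_i). Within an arm, a·g/2 is a constant.
- Student change: a·g + (e_i1 − e_i0). Within an arm, a·g is again a constant.

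A constant drops out of a slope. With arm as the grouping factor, the coefficient of cycling on the need therefore does not depend on *a*, whether averages or changes are used. The same holds for class and school means within an arm. If *a* varies between students the slope can alter, but it still does not test whether the needs moved. Reading the level (b) variables as changes repairs the second link; the first link is still not stated.

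**3. How often this could mislead (simulation A).** There were 1,500 trials per setting, with 10 schools of 51 students, variance 4.1 and ICC 0.2. The intervention raises cycling by 1.75 days by another route and has no effect on the needs; change in needs is unrelated to change in cycling. Assumed: three needs with mutual correlation 0.5, occasion noise SD 0.6, need-change ICC 0.05, and 70% of within-school cycling variance stable over time. The test was a joint 5% F-test of the three needs on students' pre/post means within school: df 3 and 510 − 10 − 3 = 497, or 3 and 255 − 5 − 3 = 247 in the intervention arm alone.

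| Assumed stable correlation | All students | Intervention arm only |
|---|---|---|
| 0 | 4.5% | not reported |
| 0.1 | 35% | 19% |
| 0.2 | 91% | 63% |
| 0.3 | 99.9% | 96% |
| 0.4 | 100% | not reported |

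Requiring both links to be significant (an 8-df school-level test of arm on change in needs, plus change on change) rejected in 0.1–0.4%.

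**4. Simulation B (400 runs, one need, five schools of 51 per arm, own assumptions).**

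- *No effect on the need, strong stable association.* The slope of 0.6 and residual SD of 1.2 imply a correlation of 0.6/√(0.36 + 1.44) = 0.45. The student-level regression was significant in 100% of runs, and the test of arm on change in the need in 5.5%.
- *Mediation only through change within students.* The effect on the need is 0.5 and the within-student slope 0.6, so the indirect effect is 0.5 × 0.6 = 0.30 days. The student-level regression was significant in about 24% of runs, and the test of arm on change in the need in 100%.

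**The case against.** The strongest reply is that this is one clause in a condensed article. A multiple-group model can yield the arm effect on the needs as a between-group difference in means or latent change, and a fuller plan may say so. Nothing in the section forbids it. This stands as a caution, but it does not remove the point. The clause is more than a promise to examine mediation: it names outcome, predictors, direction and levels, and what it names is not a mediation test.

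Three stronger readings are tempting, and the document supports none of them.

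- *Leaving out level (a) proves that change is excluded.* In a growth or latent-change model, a student's change is a student-level quantity and could sit at level (b). The text does not say whether the variables are averages, post values or changes.
- *The mediator result would almost always be positive.* That rests on assumed correlations and on an assumed test on pre/post means, which the plan does not state. At 0.1 the rate is 35%, or 19% in the intervention arm alone.
- *A two-path test errs in under 1% of trials.* Both links were null there, so about 0.05 × 0.05 = 0.25% is expected. If only the needs-to-cycling link is real, the rate can rise towards 5%.

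It is also fair that the stated aims are cycling and total activity, that the needs are called potential mediators, and that no rule for claiming mediation is given.

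**Conclusion.** The point holds in limited form. Followed as written, the analysis gives a non-randomised association between needs and cycling. It cannot support a statement about mechanisms of change, because it states neither an arm effect on the needs nor an indirect effect. That conclusion follows from the structure of the model and does not depend on the simulations. Whether change in needs is also left unrelated to change in cycling depends on what the level (b) variables are.

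The size is uncertain. With no effect on the needs, false support ranged from 35% to over 99% for assumed stable correlations of 0.1 to 0.3, under the assumed test. The document gives no value by which to choose within that range. The primary effect estimate and the required 231 students per arm are unaffected. This is a correction to a secondary analysis, worth making before the main study is analysed.

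**What to change.** Replace the mediation clause with a statement that, for each need, the analysis will:

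1. estimate the intervention-minus-control difference in pre-to-post change in the need, with arm as a school-level predictor or as a between-group difference in latent change;
2. estimate the association of change in cycling days with change in the need, adjusted for arm;
3. report the product of the two with an interval that respects school clustering and the small number of schools, for example a Monte Carlo interval with small-sample degrees of freedom (10 schools − 2 = 8). A school-level bootstrap is unreliable with about five schools per arm;
4. claim mediation only if that interval excludes 0, and note that the second link stays observational even though arm is randomised.

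Report the level (b–d) regressions as correlates of cycling. In the pilot, which is not randomised, the first link is observational too.

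The cost is wording and some extra modelling. The need questionnaires are part of both the pre- and the post-measurement, so no new data are needed. The downside is a mediation test that is less likely to be positive.

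### Mediator regressions at school level rest on five schools per arm (1 residual degree of freedom, 5 if slopes are shared), and the treatment test needs a small-sample reference

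*Protocol article*

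**What the plan says.** Under Study Design, the main trial allocates whole schools: "a simple randomization technique (i.e., flipping a coin) on school-level was chosen". The planned size is "approximately 255 students belonging to five schools with two classes in grade(s) 7 and/or 8 will be in the IG and CG, respectively", so each arm has five schools and ten classes.

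Under Statistical Analysis, effectiveness is assessed as follows: "a multiple group analysis considering the treatment factor (IG vs. CG) will be performed in a structural equation modeling". The model has four levels: repeated measurements, students, classes and, at the top, "d) the school, in which classes are nested". In a subsequent step moderators are added and "cycling to school will be regressed onto potential mediators (i.e., autonomy, competence, and relatedness) in levels (b–d". Levels b, c and d are student, class and school. Also, "gender will be considered as a covariate in the analysis"; its level is not given.

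The section names no estimator, test statistic or reference distribution. It does not say whether the mediator slopes are free in each arm or held equal.

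**The concern.** A multiple-group model estimates its parameters within each arm unless they are constrained. At the top level each arm then contributes five units, and three mediator slopes plus an intercept use up nearly all of them. The protocol article positively specifies this regression, so the point does not depend on anything left unsaid.

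Two results are at stake, for different reasons:

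- **Mechanism results.** The abstract promises insight into the mechanisms of change. School-level paths estimated on one spare degree of freedom cannot supply it, yet routine software output would attach standard errors and p-values to them.
- **The treatment comparison.** The randomised units are ten schools. Tests in structural equation modelling are usually large-sample ones (Wald z or chi-square), which are too liberal with ten units unless corrected.

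**Working it through.** **Inputs.** From Sample Size Determination: variance 4.1, difference 1.75 days per week, 51 students per school, ICC 0.2, power 80%, and a 97.5% confidence level. From Study Design: five schools per arm, two classes each. From Statistical Analysis: three mediators at student, class and school level.

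**The plan's own figure.** Students per arm = 2 × 4.1 × (1.960 + 0.842)² / 1.75² × [1 + (51 − 1) × 0.2] = 21.016 × 11 = 231.2. This reproduces the stated 231, reading the 97.5% as the normal quantile of a two-sided 5% test. Dividing by 51 gives 4.53 schools, rounded up to five schools, or 255 students. The calculation uses normal quantiles only.

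**Mediator regressions: residual degrees of freedom**

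| Level | Units | Parameters | Residual df |
|---|---|---|---|
| School, paths free in each arm | 5 per arm | 1 intercept + 3 slopes | 5 − 4 = 1 per arm |
| School, slopes equal across arms | 10 | 2 intercepts + 3 slopes | 10 − 5 = 5 |
| Class within school, paths free | 5 contrasts per arm | 3 slopes | 5 − 3 = 2 per arm |
| Student within class, paths free | 255 per arm | 10 class means + 3 slopes | 255 − 13 = 242 per arm |

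The count treats school and class means of the mediators as known. Only the student level carries real information.

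**Actual two-sided error of a nominal 5% test of a school-level path.** With an unbiased variance this is P(|t| > 1.96) on the residual df. With a maximum-likelihood (ML) variance the cut-off shrinks by √(df/n).

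- 1 df (n = 5): t critical value 12.7. Error is 0.30 with unbiased variance, 0.54 with ML variance and z (cut-off 1.96 × √(1/5)), and 0.48 with the ML likelihood-ratio test.
- 5 df (n = 10): t critical value 2.57. Error is 0.107 with unbiased variance, 0.224 with ML variance and z (cut-off 1.96 × √(5/10)), and 0.186 with the likelihood-ratio test.

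**Treatment contrast, five versus five schools (10 − 2 = 8 df)**

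- Unbiased variance with z: P(|t₈| > 1.96) = 0.086.
- ML variance with z: P(|t₈| > 1.96 × √(8/10)) = 0.118.
- ML likelihood-ratio test: 0.089.
- Simulation of 200,000 null trials (ten schools of 51, ICC 0.2): 0.085 with unbiased variance and 0.118 with ML variance. Estimating the variance separately in each arm gives 0.085 and 0.117.

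**Power on 8 df.** Variance of a school mean = 4.1 × 11 / 51 = 0.884. Standard error of the difference = √(2 × 0.884 / 5) = 0.595. Then 1.75 / 0.595 = 2.94. Power is 83.7% by the normal approximation and 73.2% with the t(8) critical value of 2.306.

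**The case against.** The best case for the plan has several parts.

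- **The error rate rests on unstated choices.** No estimator or reference distribution is named, and an article may leave a small-sample correction to the analysis plan. This stands. The 8.6% to 11.8% applies only if uncorrected large-sample tests are used.
- **The calculation is simpler than the planned model.** It compares school means at one time point, whereas the plan has repeated measurements within four levels. This also stands. The true figure could be lower or higher, depending partly on whether school-by-time variation is modelled.
- **The mediators come later.** A reader might infer that the shortage of school-level degrees of freedom is what inflates the treatment test. It is not: the mediators enter in a subsequent step, and the treatment test has its own separate small-sample problem.
- **The school-level paths can still be estimated.** A reader might call them non-estimable. In the main study that is too strong, since one degree of freedom gives an estimate and equal slopes give five. Adding a school-level moderator (educational level or region, Table 4) to free paths would remove the last degree of freedom, but the text assigns moderators to no level.
- **The pilot.** With "approximately 150 students belonging to three schools will be in the IG and 100 students belonging to two schools in the CG", one might infer that the pilot cannot fit the model. The article does not assign this model to the pilot. The Discussion ties the pilot to the planned organisational procedure and measuring instruments, so no claim about it is made here.

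None of this rescues the school-level mediator regressions. The number of schools and the levels of the regressions are both fixed in the text, and no choice of estimator adds schools.

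**Conclusion.** The point holds in two separate parts of different strength.

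The first follows directly from the text. Regressing cycling on three mediators at school level, with five schools per arm, gives coefficients that are essentially uninformative and large-sample tests of them that are seriously miscalibrated, even on the more favourable reading of shared slopes. The class level is little better. This affects the mechanism analysis and not the estimate of the primary effect.

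The second is conditional. If the treatment effect is judged by the usual uncorrected tests, the nominal 5% level becomes about 1.7 to 2.4 times too large (0.086/0.05 to 0.118/0.05). This assumes five equally sized schools per arm, normally distributed school means and a single post-intervention contrast. It illustrates the size of the problem and is not a prediction for the four-level model. That the treatment test will certainly reject too often is not something the document establishes.

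**What to change.** 1. Restrict the mediator regressions to student level, with mediators centred on their cluster means, and remove them from class and school level.
2. State a small-sample reference for the treatment effect. One option is a single mixed model pooled across arms for post-intervention cycling days, with arm, baseline cycling days and gender as fixed effects, random intercepts for school and class, and Kenward-Roger or Satterthwaite degrees of freedom. A school-level t test or permutation test would also serve. Structural equation modelling can remain for the student-level mediation.
3. Restate power on 8 df and review whether five schools per arm are enough.

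The rewording is short and the software standard. The real costs are wider intervals, giving up any school-level mediation claim, and acknowledging that power for 1.75 days is below the planned 80% before any gain from baseline adjustment. That gain cannot be sized from the article, which gives no correlation between pre- and post-measurements. If it proves insufficient, more schools would be needed.
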